**Supplementary Figure S1: Flow diagram summarizing the process of the trial**

Identify patient with post-stroke depression

Check eligibility

Consent

**Collect baseline data**: physical exam, vital signs, computerized cognitive tests, questionnaires, psychiatric assessment, blood samples.

Start treatment with 300 mg/day Maraviroc

**Follow-up assessment on week 2 and weeks 4, 7, and 10:** physical exam, vital signs, computerized cognitive tests (at week 10), questionnaires, psychiatric assessment, record of AEs related or not related to the medication assignment, concomitant medications, pill counts, blood samples.

**Telephone contact assessment on weeks 3, 5, 8, and 9:** record of AEs, and concomitant medications.

**Follow-up assessment on weeks 14, and 18 (post-treatment assessments):** physical exam, vital signs, questionnaires, psychiatric assessment.

Supplemental Methods: Sample size calculation

The percentage of pilot study participants who tolerate a new treatment or the proportion of eligible patients who provide informed consent for participation would be representative of the tolerance or participation rates if all potential participants were studied. Providing a means to estimate these quantities enables early indicators of treatment tolerability and enrollment feasibility.

Weight gain and sexual dysfunction are well documented with the current anti-depressants, usually selective serotonin reuptake inhibitors (SSRIs) or Serotonin-Norepinephrine Reuptake Inhibitors (SNRIs). Another side effect of SSRIs is hyponatremia, which can limit their use in stroke patients.

It is of clinical interest to identify augmentative therapies that can alleviate some of the known side effects affecting a high percentage of patients receiving SSRIs or SNRIs (an average of 30% of people treated with an SSRI reported sexual dysfunction^1^, while 25% of individuals had a significant body weight increase^2^ and an average of 22% had hyponatremia^3^). Therefore, it is desirable to rule out potential treatments not consistent with this rate of sexual dysfunction, weight gain, and hyponatremia before considering more conclusive testing. Using the following equation,

**
[figure not shown]
**

(where π is the probability of the adverse event of interest)

we would conclude that the augmentative therapy has sexual dysfunction rates less than 0.31, at the 90% confidence level, if a total of 10 patients are recruited and all 10 do not experience sexual dysfunction. We would conclude that the augmentative therapy has weight gain rates less than 0.25, at the 90% confidence level, if a total of 8 patients are recruited and all 8 do not experience weight gain. We would conclude that the augmentative therapy has hyponatremia rates less than 0.22, at the 90% confidence level, if a total of 9 patients are recruited and all 9 do not experience weight gain. Therefore, an initial sample size of 10 patients would be sufficient to identify augmentative therapies, such as Maraviroc. The results of such a pilot study could then be used to rank-order Maraviroc as a potential therapy thereby proving an empirically justified approach to therapy development.

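### The three zero-event bounds behind n = 10 do not share one 90% confidence level: 0.31 should be 0.206, and 0.22 is narrowly missed with 9 patients

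*Protocol*

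**What the plan says.** The Protocol section on sample size calculation (Supplemental Methods) takes three side-effect rates under current antidepressants as references:

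- sexual dysfunction: "an average of 30% of people treated with an SSRI reported sexual dysfunction"
- weight gain: "25% of individuals had a significant body weight increase"
- hyponatremia: "an average of 22% had hyponatremia"

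It then refers to an equation, which is a figure missing from the text at hand; only its parameter is defined ("where π is the probability of the adverse event of interest"). From the equation it draws three conclusions, each for the case in which no patient has an event:

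- "sexual dysfunction rates less than 0.31, at the 90% confidence level, if a total of 10 patients are recruited"
- "weight gain rates less than 0.25, at the 90% confidence level, if a total of 8 patients are recruited"
- "hyponatremia rates less than 0.22, at the 90% confidence level, if a total of 9 patients are recruited"

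The hyponatremia sentence ends with the condition that "all 9 do not experience weight gain". The section concludes that 10 patients are enough.

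**The concern.** The three statements carry the same confidence label and the same event count, zero, so they should lie on one curve: the more event-free patients, the lower the bound. Ordered by n, the printed bounds are 0.25 (n = 8), 0.22 (n = 9) and 0.31 (n = 10). The last step goes the wrong way, so at least one figure cannot be the 90% bound for its n, whatever the missing equation is.

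The section exists to show that 10 patients can separate the new treatment from the reference rates, and it is the protocol's only quantitative support for n = 10. A bound of 0.31 lies above the 30% reference, so the sexual-dysfunction statement as printed does not do that job. The hyponatremia statement implies that 9 evaluable patients would be enough for 22%, which leaves one to spare. It also makes a conclusion about hyponatremia depend on the absence of weight gain, which carries no information about hyponatremia.

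**Working it through.** **Inputs** (all from the sample-size section): bound and n of 0.31 and 10, 0.25 and 8, 0.22 and 9; confidence 90%; zero events; reference rates 30%, 25% and 22%.

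**Formulas** (inferred, because the equation is not shown). With zero events in n patients:

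- upper bound = 1 − (1 − conf)^(1/n)
- confidence attained for a stated bound π = 1 − (1 − π)^n
- n required = ln(1 − conf) / ln(1 − π), rounded up

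**Step 1: reproduce a printed figure.** Weight gain: 1 − 0.10^(1/8) = 0.2501, and 0.75^8 = 0.1001. The printed 0.25 with n = 8 is therefore the exact one-sided 90% bound to rounding (attained confidence 89.99%). This pair identifies the likely rule.

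**Step 2: apply the same rule to all three.**

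| Event | n | Printed bound | One-sided 90% bound | Confidence attained by printed bound | n needed at 90% for printed bound |
|---|---|---|---|---|---|
| Weight gain | 8 | 0.25 | 0.250 | 89.99% | 8.004, i.e. 8 to rounding |
| Hyponatremia | 9 | 0.22 | 0.226 | 1 − 0.78^9 = 89.3% | 9.27, so 10 |
| Sexual dysfunction | 10 | 0.31 | 0.206 | 1 − 0.69^10 = 97.6% | 6.21, so 7 |

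**Step 3: try other conventions.** Exact bounds for n = 10 / 8 / 9 are:

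- one-sided 95%: 0.259 / 0.312 / 0.283
- one-sided 97.5%: 0.308 / 0.369 / 0.336

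The rule of three, Wilson, Agresti-Coull, Jeffreys, uniform-prior and mid-P bounds were also tried. None gives 0.31, 0.25 and 0.22 together. Two other conventions also give 0.25 at n = 8, to rounding:

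- two-sided 90% mid-P, which coincides with the exact one-sided 90% bounds above
- two-sided 90% Wilson, with 0.213 / 0.253 / 0.231

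Under either of these, 0/10 lies below 22% and 0/9 does not, as under the exact rule.

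**Step 4: compare with the reference rates.** With all 10 patients event-free, the one-sided 90% bound is 0.206 for each event: below 0.30, 0.25 and 0.22. With 9 evaluable and event-free it is 0.226: below 0.30 and 0.25, but not 0.22. The printed 0.31 exceeds 0.30.

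**The case against.** The best defence is that the sexual-dysfunction sentence is not false. If the rate is below 0.206 with 90% confidence, it is also below 0.31 with at least 90% confidence. That stands: the figure is loose and mislabelled, not anti-conservative, and correcting it strengthens the sponsor's argument.

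The hyponatremia gap is small: 89.3% against 90%, or 10 patients against 9, and the trial enrols 10. The wrong event name is evidently a copying slip, since the same sentence names hyponatremia as the rate being bounded. Both points stand and limit the weight of the finding.

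The formula is inferred because the equation is not visible. That qualifies the corrected values but not the inconsistency, since the rise from n = 9 to n = 10 is visible without any formula. The origin of 0.31 is unknown. It is close to the one-sided 97.5% bound for 0/10 (0.308), but the one-sided 95% bound for 0/8 (0.312) also rounds to it.

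A reader might infer three stronger things that the protocol does not support:

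- **That 10 patients are too few.** At exact one-sided 95%, 0/10 gives 0.259, which excludes neither 25% nor 22%. But the protocol's own pair of 0.25 with 8 patients does not fit that level, which gives 0.312; it fits one-sided 90%.
- **That a go/no-go rule is wrong.** The section says only that results could help rank the therapy. The Design section makes further research depend on the drug proving safe, and the primary safety endpoint is about serious events and events leading to discontinuation. The Statistical Analysis section has no rule on these three side effects.
- **That the weight-gain statement also fails.** 0.2501 against 0.25 is rounding.

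**Conclusion.** The point holds as an error in the sample-size rationale. The three statements cannot all be 90% bounds under one rule. On the one-sided 90% rule that the weight-gain pair implies, the sexual-dysfunction bound is 0.206 instead of 0.31, the only large discrepancy. It matters because the printed value does not exclude the 30% reference rate while the correct value does. The hyponatremia bound is 0.226 instead of 0.22, a narrow miss, and its condition names the wrong event.

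The sample size of 10 survives, since 0.206 is below all three reference rates. For 22%, however, there is no spare patient: if one of the 10 is not evaluable, an event-free result no longer excludes that rate at 90%. The verdict rests on the inferred zero-event formula and on reading 90% as one-sided. No planned analysis in the protocol depends on these bounds.

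**What to change.** Replace the three sentences with one statement, for example: *With 10 evaluable patients and no event, the one-sided 90% upper limit is 20.6% for each event, below the reference rates of 30%, 25% and 22%; with 9 evaluable patients it is 22.6%, which does not exclude 22%.* In any sentence kept on hyponatremia, change the condition from weight gain to hyponatremia.

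The cost is wording only: n stays at 10, and the endpoints and analyses are untouched.

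### The sexual-dysfunction bound for 0 of 10 events is printed as 0.31 at 90% confidence. The formula that reproduces the weight-gain bound gives 0.206, and the trial size of 10 is unaffected.

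*Protocol*

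**What the plan says.** The Protocol, under Supplemental Methods: Sample size calculation, justifies ten patients by what an event-free series would show about three known antidepressant side effects. The reference rates are 30% for sexual dysfunction ("an average of 30% of people treated with an SSRI reported sexual dysfunction"), 25% for weight gain and 22% for hyponatremia. The stated aim is that "it is desirable to rule out potential treatments not consistent with this rate of sexual dysfunction, weight gain, and hyponatremia".

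The section refers to one equation, of which only the definition of its parameter is visible ("where π is the probability of the adverse event of interest"). It then gives three conclusions, each for a series without events:

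- "sexual dysfunction rates less than 0.31, at the 90% confidence level, if a total of 10 patients are recruited"
- "weight gain rates less than 0.25, at the 90% confidence level, if a total of 8 patients are recruited"
- "hyponatremia rates less than 0.22, at the 90% confidence level, if a total of 9 patients are recruited"

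From these it concludes that "an initial sample size of 10 patients would be sufficient to identify augmentative therapies".

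**The concern.** Two features of the sexual-dysfunction line look wrong before any formula is chosen. First, it has the most patients of the three and the highest bound. With no events and a fixed confidence level, adding patients can only lower the upper bound. Second, the other two bounds equal their reference rates (0.25 against 25%, 0.22 against 22%), whereas 0.31 lies just above its reference of 30%. Read literally, a perfect result in all ten patients would stop short of excluding the rate it is compared with.

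At stake is the accuracy of the only sample-size justification in the protocol. The sexual-dysfunction line is also the only one stated for the full ten patients. A reader who takes 0.31 at face value would misjudge what an event-free trial shows.

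**Working it through.** **Inputs**, all from the sample size section: zero events in each case; n = 10, 8 and 9; confidence 90%; stated bounds 0.31, 0.25 and 0.22; reference rates 0.30, 0.25 and 0.22. The hyponatremia sentence names weight gain in its event-free condition; I read it as no hyponatremia.

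**Formula (inferred).** With π the event probability, the chance of no events in n patients is (1 − π)^n. Setting this to 1 − C, where C is the one-sided confidence, gives the upper bound π_U = 1 − (1 − C)^(1/n).

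**Step 1: reproduce a stated figure.** For weight gain, 1 − 0.1^(1/8) = 0.2501, which matches the stated 0.25. This supports the exact one-sided 90% bound as the method in use.

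**Step 2: apply it to all three.**

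| Event | n | Stated | 1 − 0.1^(1/n) | Reference rate |
|---|---|---|---|---|
| Weight gain | 8 | 0.25 | 0.250 | 0.25 |
| Hyponatremia | 9 | 0.22 | 0.226 | 0.22 |
| Sexual dysfunction | 10 | 0.31 | 0.206 | 0.30 |

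The sexual-dysfunction figure is too high by 0.31 − 0.206 = 0.104, about 50% in relative terms (0.31/0.206 = 1.50). The hyponatremia figure misses slightly: 0.226 rounds to 0.23.

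**Step 3: look for any 90% method that gives 0.31 for 0 of 10.**

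- Exact, two-sided 90%: 1 − 0.05^(1/10) = 0.259. The same reading gives 0.312 for 0 of 8, which breaks the weight-gain match.
- Wilson: 0.141 one-sided, 0.213 two-sided.
- Agresti-Coull: 0.167 and 0.249.
- Jeffreys: 0.124 and 0.171.
- Approximation −ln(0.1)/10: 0.230.

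None gives 0.31.

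**Step 4: find the confidence that does go with 0.31.** 1 − 0.69^10 = 1 − 0.0245 = 97.6%. Conversely, the one-sided 97.5% bound for 0 of 10 is 1 − 0.025^(1/10) = 0.3085, which rounds to 0.31.

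**Step 5: check what 0 of 10 says about 30%.** 0.7^10 = 0.028, well below 0.10. So 0 of 10 excludes 30% at one-sided 90%.

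**Step 6: patients needed to exclude each reference rate at one-sided 90%**, ln(0.1)/ln(1 − π):

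- 0.30: 6.46, so 7.
- 0.25: 8.004, so 8 to the rounding used in the protocol (0.75^8 = 0.1001).
- 0.22: 9.27, so 10.

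Ten event-free patients give 0.206, which is below all three reference rates.

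**The case against.** The strongest reply is that the error does no harm. A rate shown to be below 0.206 is also below 0.31, so the printed sentence understates what 0 of 10 supports and makes no excessive safety claim. Seven event-free patients would already exclude 30% at this level, so ten is ample for this event. Nothing downstream depends on the figure: the primary safety endpoint concerns serious treatment-emergent events and those leading to discontinuation, the safety analysis is descriptive, and neither the Statistical Analysis nor the Safety Plan refers to a sexual-dysfunction bound. All of this stands, and it limits the severity.

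A second reply is that the equation cannot be seen, so the method is an inference, and that the inferred formula does not reproduce the hyponatremia figure exactly. That is fair, and the assumption is stated here. It does not rescue 0.31. None of the 90% methods tried gives it, and the ordering of the three bounds is impossible under any single method and level whose bound falls with n.

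A reader might go further and infer that the trial cannot exclude a 30% rate, or that ten patients are too few. The documents do not support that. Only the printed bound fails to clear 30%, by 0.01; the result it describes, 0 of 10, excludes 30% with about 97% confidence (1 − 0.028).

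**Conclusion.** The figure 0.31 is wrong as a 90% bound for 0 of 10. The value consistent with the weight-gain statement is 0.206, and even the two-sided reading gives only 0.259; both are below 30%. The printed figure overstates the bound by about 0.10 and places it on the wrong side of the reference rate. The hyponatremia figure is off by a much smaller amount (0.226 against 0.22).

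Severity is moderate. The sexual-dysfunction error is conservative and confined to the sample-size justification, and the trial size of 10 stands. The value 0.206 assumes the exact one-sided zero-event bound, inferred from the match at n = 8. The finding that 8, 9 and 10 patients cannot yield 0.25, 0.22 and 0.31 needs only one common method and confidence level. Whether 0.31 came from a 97.5% calculation or is a slip for 0.21 cannot be told from the document, and the point does not depend on it.

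**What to change.** Replace 0.31 with 0.206 (0.21), label it as a one-sided 90% upper bound for 0 of 10, and state that it lies below the 30% reference rate.

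Apply the same formula to all three events. Weight gain is unchanged at 0.25 for 0 of 8. For hyponatremia, either restate the bound for 0 of 9 as 0.23, or use 0 of 10, which gives 0.206. The second choice is better: 0.226 is still above the 22% reference, whereas 0.206 is below it, and it shows why ten patients are wanted. The condition in that sentence should also name hyponatremia.

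Do not repair the text by keeping 0.31 and relabelling it as 97.5%. At that level 0 of 8, 0 of 9 and 0 of 10 give 0.369, 0.336 and 0.309, all above their reference rates of 0.25, 0.22 and 0.30, and the argument for ten patients would fail.

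The cost is two edited sentences in the sample size section. The trial size, endpoints and analyses do not change.

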# We plan to perform a proof-of-concept open label add-on clinical trial of 300 mg Maraviroc given once daily for 10 weeks in 10 patients with PSD. Depression scores over time will serve as outcome measures and each patient function will be compared before and after treatment with study drug, beyond current treatment with other anti-depressants, such that the efficacy will be analyzed only beyond the efficacy of current treatments. The study will consist of 3 phases: (1) screening, (2) open-label treatment (weeks 1-10), and (3) post-treatment follow-up (8 weeks). The primary objective will be safety and tolerability of Maraviroc 300 mg per day in subjects with PSD. If proved safe, we plan continued research to establish efficacy using different dosages of Maraviroc

Objectives

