**Overview of Study Design**

This is a proof-of-concept, open-label, single center study conducted in 10 male and female adult subjects with PSD. Each subject will participate in 3 phases: (1) a screening phase of up to 1 week, (2) an open-label treatment phase of 10 weeks, and (3) an 8-week post-treatment (follow up) phase. The end of study will occur when the last subject in the trial completes his/her last study assessment.

Screening and Baseline assessments

After giving informed consent, subjects will be screened to determine eligibility for study participation. Note: Subjects who are not currently taking an antidepressant at screening are eligible to participate in this study (i.e., subjects may participate in the study whether or not they are taking an antidepressant). Subjects who are taking an antidepressant at the screening visit must have been receiving a stable dose (i.e., dose has been unchanged for at least 2 months before the screening visit) and will be guided to continue the antidepressant at the same dose during the treatment phase. All adverse events and special reporting situations, whether serious or non-serious, will be reported from the time a signed and dated informed consent form (ICF) is obtained until completion of the subject's last study-related procedure (which may include contact for follow-up of safety). If a subject withdraws before the end of the treatment phase for reasons other than withdrawal of consent, the early termination visit should be conducted at the time of discontinuation, followed by completion of the posttreatment phase. All subjects will self-administer the study medication.

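### The weight-gain rule sets a 10-week count against a 25% rate with no stated time window, so 0 of 8 does not show an advantage over current antidepressants

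*Protocol*

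**What the plan says.** The Supplemental Methods section on sample size takes three side-effect rates on current antidepressants as benchmarks and gives, for each, the number of event-free patients needed to conclude that the rate on Maraviroc is lower. For weight the benchmark is that "25% of individuals had a significant body weight increase". The rule reads "We would conclude that the augmentative therapy has weight gain rates less than 0.25". The confidence attached to this statement is 90%, and the condition for making it is given as "if a total of 8 patients are recruited and all 8 do not experience weight gain". The same section says that the pilot results could then be used to rank Maraviroc as a candidate therapy.

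The only source given for the 25% is reference 2 of that section, titled "Antidepressant utilisation and incidence of weight gain during 10 years' follow-up: population based cohort study". The protocol does not state the period over which the 25% arose.

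The trial's own observation time is fixed elsewhere. The Design section describes "300 mg Maraviroc given once daily for 10 weeks in 10 patients with PSD", and the Overview of Study Design repeats "an open-label treatment phase of 10 weeks". In Table S1 the body-weight row is marked from screening to week 10, with no mark at weeks 14 and 18.

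**The concern.** A cumulative risk has meaning only together with the time over which it accrues. The rule uses 25% as the rate that a treatment must beat, but the trial counts events over 10 weeks and makes no adjustment for the benchmark's exposure period. If that period is longer than 10 weeks, a treatment that causes weight gain exactly as often as the benchmark antidepressants has a 10-week risk well below 25%. It will then often show no events among 8 patients.

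The stated 90% confidence suggests that a treatment no better than the benchmark would pass about one time in ten. If the true figure is several times higher, a clean result says little about whether Maraviroc compares well with SSRIs or SNRIs on weight. That comparison is the purpose of the rule and the basis for the proposed ranking.

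**Working it through.** **Inputs.** From the sample size section: benchmark 0.25, 8 patients, zero events, 90% confidence. From the Design section: 10 weeks of treatment. Assumptions, because the protocol gives neither: the length Y (in years) of the period over which the 25% accrues, and a constant hazard over that period. A year is taken as 52.18 weeks.

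**1. The plan's own figure.** The equation is not legible in the text available, so the usual zero-event form is assumed: (1 − π)^n = 0.10.
- n = ln(0.10) / ln(0.75) = 8.004, which the plan gives as 8.
- Check: 0.75^8 = 0.1001.
- One-sided 90% upper limit for 0 of 8: 1 − 0.10^(1/8) = 0.2501.

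The figure reproduces on the one-sided reading. A two-sided 90% interval would need n = ln(0.05) / ln(0.75) = 10.4. So 0 of 8 does bound the *10-week* rate at about 0.25.

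**2. What the benchmark implies at 10 weeks.** With a constant hazard,

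q = 1 − 0.75^(10 / (52.18 × Y)) and P(0 of n) = (1 − q)^n.

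Example for Y = 10: 10 / 521.8 = 0.01916; 0.75^0.01916 = 0.9945; q = 0.0055; P(0 of 8) = 0.9945^8 = 0.957.

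| Period over which the 25% accrues (assumed) | 10-week risk q | P(0 of 8) | P(0 of 10) |
|---|---|---|---|
| 10 weeks | 25% | 10% | 6% |
| 0.5 year | 10.4% | 41% | 33% |
| 1 year | 5.4% | 64% | 58% |
| 2 years | 2.7% | 80% | 76% |
| 5 years | 1.1% | 92% | 90% |
| 10 years | 0.55% | 96% | 95% |

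Every row describes a treatment with exactly the benchmark hazard. The nominal 10% appears only in the first row, where the whole 25% arises within 10 weeks.

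**3. Does the rule respond to the drug?** For a given 10-week risk p, P(0 of 8) = (1 − p)^8:
- p = 5%: 66%
- p = 10%: 43%
- p = 20%: 17%
- p = 25%: 10%

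It does respond to a strong short-term effect. On the 10-year reading, however, a treatment that triples the benchmark hazard still gives 0 of 8 with probability 0.75^(3 × 80 / 521.8) = 88%, and one that raises it tenfold with probability 0.75^(10 × 80 / 521.8) = 64%.

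**The case against.** The case on the other side is substantial and limits the point.

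- **The literal conclusion can be true.** A 10-week rate below 0.25 is what 0 of 8 supports. This stands: the statement is not false, but it does not answer the comparison with antidepressants.
- **The accrual period is unknown.** A study's length of follow-up does not prove that the 25% is a ten-year cumulative risk, and weight gain may be concentrated early in treatment. This also stands. A reader might infer that the rule is almost certain to be met, but 96% is only the far end of the range, and shorter accrual periods give 41% to 80%.
- **The rule is not blind.** A reader might infer that the result would be the same whatever Maraviroc does. Step 3 shows otherwise.
- **The missing threshold is not the point.** The rule speaks of weight gain without a kilogram or percentage cut-off, and a reader might infer that any upward fluctuation counts, so that the rule could hardly ever be met. That reading is strained, because the phrase follows directly on the benchmark's significant increase. A cut-off may also sit in a statistical analysis plan that is not at hand.
- **One event does not fail the drug.** The text says only what would be concluded with no events and gives no rule for one or more.
- **The weight rule is not an endpoint.** The primary safety endpoint concerns serious treatment-emergent events and those leading to discontinuation. The Statistical Analysis section only tabulates safety data, and the ranking sentence is conditional. This limits the importance of the point but does not remove it, because the protocol still states the conclusion without qualification.

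None of this supplies a time window for the 25%. An analysis plan could not repair the mismatch by defining the event alone, since the benchmark, its source and the conclusion are all fixed in the protocol's sample size text.

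**Conclusion.** The concern holds as a mismatch of time horizon. The upper limit of 0.25 is correct for a 10-week rate, but a clean 0 of 8 does not show that Maraviroc compares favourably with the antidepressant benchmark. Over assumed accrual periods of 0.5 to 10 years at constant hazard, a treatment no better than the benchmark would give 0 of 8 with probability 41% to 96%. Even the lower end is about four times the nominal 10%. The nominal figure is recovered only if the whole 25% arises within about 10 weeks, which the protocol neither states nor supports.

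The size depends on the two assumptions, accrual period and constant hazard. The direction depends only on the benchmark period being longer than 10 weeks, which the title of the cited source suggests but does not prove. The effect is on what the trial may claim about weight. The primary safety endpoint and the sample size are not affected.

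**What to change.** Choose one of two changes to the sample size section:

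1. Replace the 25% with a reference rate for the same weight-gain event over about 10 weeks of exposure, state the event and the period, and recompute the number of event-free patients from it.
2. If no such rate is available, delete the conclusion that the rate is below 0.25 and its use in ranking Maraviroc.

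In either case, report the 10-week count of weight-gain events with an exact confidence interval and the mean weight change from Day 1 to week 10 with its interval, and describe both as 10-week data only.

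The cost is wording. Weight is already scheduled up to week 10, so no visit or measurement is added. The total of 10 need not change under the second option, because the sexual-dysfunction case sets it and the weight case asks for only 8. Under the first option, a lower 10-week reference rate would call for more event-free patients than 8. If that number exceeds 10, the claim should be dropped rather than the trial enlarged. The downside is the loss of one favourable tolerability claim.

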# This study will evaluate the safety and efficacy of Maraviroc 300 mg per day in patients suffering from PSD.

Primary objective:

1. To investigate the safety and tolerability of Maraviroc 300 mg per day in subjects with PSD.

Secondary Objectives:

1. To investigate the safety and tolerability of Maraviroc 300 mg in PSD subjects, with special attention to: effects on heart rate and blood pressure.
2. To evaluate the efficacy of Maraviroc 300 mg per day in improving depressive symptoms in subjects with PSD, as assessed by a change from baseline in the Montgomery-Asberg Depression Rating Scale (MADRS) total score and in improving cognitive, functional, and behavioral outcomes.

To evaluate the effect of treatment with Maraviroc 300 mg per day for 10 weeks on blood inflammatory markers in subjects with PSD.

3. To assess the effect of Maraviroc 300 mg in PSD subjects on: a. Depressive symptoms, as assessed by the 16-item Quick Inventory of Depressive Symptomatology- Self Report (QIDS-SR16) b. Remission, defined as a MADRS total score ≤10 c. Response, defined as a ≥50% reduction from baseline in MADRS total score d. The severity of illness using the Clinical Global Impression - Severity (CGI-S) and the Patient Global Impression - Severity (PGI-S) e. Symptoms of anxiety as assessed by the Generalized Anxiety Disorder 7-item Scale (GAD-7). d. Cognitive status, as assessed by cognitive score based on repeatable computerized battery of cognitive tests (Neurotrax) and Montreal Cognitive Assessment (MoCA). e. Functional outcome, as assessed by the stroke impact scale (SIS), the activities of daily living (ADL) score, and Reintegration to Normal Living Index (RNL).

Methods

We plan to enroll ten adults with PSD.

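### Nine event-free patients give a 90% upper limit of 0.226 for hyponatremia, not below 0.22; ten are needed, and the same sentence names the wrong event

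*Protocol*

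**What the plan says.** The section Supplemental Methods: Sample size calculation takes three side effect rates from the antidepressant literature and treats them as benchmarks to be ruled out. For hyponatremia the benchmark is "an average of 22% had hyponatremia". For each side effect the section then gives a number of patients who must all be event-free:

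- Sexual dysfunction: "sexual dysfunction rates less than 0.31, at the 90% confidence level, if a total of 10 patients are recruited". The cited rate is 30%.
- Weight gain: "weight gain rates less than 0.25, at the 90% confidence level, if a total of 8 patients are recruited". The cited rate is 25%.
- Hyponatremia: "hyponatremia rates less than 0.22, at the 90% confidence level, if a total of 9 patients are recruited", with the condition that "all 9 do not experience weight gain".

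From these the section concludes that "an initial sample size of 10 patients would be sufficient to identify augmentative therapies". The Methods section agrees: "We plan to enroll ten adults with PSD".

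The equation behind the rules is a figure that is not reproduced in the available text; only its symbol for the probability of the adverse event is explained.

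**The concern.** The hyponatremia rule is a strict inequality with a stated confidence level, so it can be checked directly. If nine event-free patients leave an upper limit above 0.22, the rule allows a conclusion that the data do not support at the stated confidence. This matters only when nine patients are evaluable and none has hyponatremia. By the written rule the report could then say that the 22% benchmark is excluded, although the 90% limit still contains it. Hyponatremia is also the side effect that the Introduction singles out as limiting the use of SSRIs in elderly patients and stroke survivors.

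The sentence has a second fault. Its conclusion is about hyponatremia, but its condition is the absence of weight gain. Read literally, it infers one event rate from the absence of another event.

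**Working it through.** **Inputs, all from the sample size section.** Benchmark π = 0.22; confidence 90%; 0 events; n = 9. The companion rules are 0 of 8 for 0.25 and 0 of 10 for 0.31.

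**Assumed method.** With zero events in n patients, the exact one-sided 90% upper limit is U = 1 − 0.10^(1/n). The confidence attached to a benchmark π is 1 − (1 − π)^n. The smallest adequate n is ln(0.10)/ln(1 − π), rounded up. This form is inferred, because the equation is not shown.

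**Reproducing the plan's own figure first.** For weight gain, 1 − 0.10^(1/8) = 0.2501, and 1 − 0.75^8 = 0.8999. This matches the stated 0.25 at 90% to rounding, which supports the inferred method.

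**The hyponatremia rule by the same method.**

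- U for 0 of 9 = 1 − 0.10^(1/9) = 0.2257, which is above 0.22 and rounds to 0.23.
- Confidence for 0.22 = 1 − 0.78^9 = 1 − 0.1069 = 0.8931, or 89.3%.
- Required n = ln(0.10)/ln(0.78) = 9.27, so 10.
- U for 0 of 10 = 1 − 0.10^(1/10) = 0.2057; confidence for 0.22 = 1 − 0.78^10 = 0.9166, or 91.7%.

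**Would another method rescue the nine?** It would have to give about 0.25 for 0 of 8 and less than 0.22 for 0 of 9.

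| Method (upper limit) | 0 of 8 | 0 of 9 |
| --- | --- | --- |
| Exact, one-sided 90% | 0.250 | 0.226 |
| Exact, two-sided 90% | 0.312 | 0.283 |
| ln(10)/n | 0.288 | 0.256 |
| 3/n | 0.375 | 0.333 |
| Wilson, two-sided 90% | 0.253 | 0.231 |
| Wilson, one-sided 90% | 0.170 | 0.154 |
| Jeffreys, one-sided 90% | 0.151 | 0.136 |
| Jeffreys, two-sided 90% | 0.208 | 0.187 |
| Mid-p, one-sided 90% | 0.182 | 0.164 |
| Uniform-prior Bayes, one-sided 90% | 0.226 | 0.206 |

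None does both. The methods that fall below 0.22 for nine patients do not give 0.25 for eight.

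**The companion rules on the same basis.**

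- Sexual dysfunction: 0 of 10 gives 0.206, not 0.31. The stated 0.31 instead matches 1 − 0.025^(1/10) = 0.3085, the upper end of a two-sided 95% interval. At one-sided 90%, seven event-free patients would already suffice for 0.30 or 0.31 (0 of 7 gives 0.280).
- Weight gain: 0.2501 is not strictly below 0.25. Strictly, n = ln(0.10)/ln(0.75) = 8.004, so 9.

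**The case against.** The best defence is that nothing in the trial changes. The section adopts ten patients, and 0 of 10 does exclude 0.22. The shortfall is one patient in an intermediate figure and 0.7 percentage points of confidence (90 − 89.3). The primary safety endpoint concerns serious adverse events and adverse events leading to discontinuation, and the Statistical Analysis section summarises safety in tables; neither uses the hyponatremia benchmark. All of this stands, and it makes the point minor. It does not make the sentence correct.

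The method is also inferred. It matches the 8-patient rule but not the 10-patient rule, so the three rules do not share one basis. That limits certainty about the intended formula. However, no method tried above yields both 0.25 for eight patients and less than 0.22 for nine.

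Two stronger readings are tempting. A reader might infer that a need for nine out of ten enrolled means the protocol claims a patient to spare. It does not: the three rules give 10, 8 and 9, the plan takes the largest, and the sexual dysfunction rule already uses all ten.

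A reader might also infer from the word recruited that an early dropout with no later blood sample counts as event-free. That reading is strained, since the rule requires patients not to experience the event, which presupposes that the outcome is observed. The Overview of Study Design adds: "If a subject withdraws before the end of the treatment phase for reasons other than withdrawal of consent, the early termination visit should be conducted". The definition of the evaluable denominator is commonly left to the statistical analysis plan, which is not at hand. For the same reason it cannot be said that any single dropout removes the conclusion, because a patient who withdraws may still provide sodium values.

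**Conclusion.** The hyponatremia rule is wrong as written, and the error is minor. Under the one-sided zero-event bound, nine event-free patients give an upper limit of 0.226 at 90%, or 89.3% confidence for 0.22. Ten are needed, and they give 0.206 and 91.7%. The condition in the same sentence names weight gain where hyponatremia is meant.

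The planned enrolment of ten remains adequate for this benchmark, provided that all ten are evaluable and event-free. With nine evaluable and event-free, the 22% rate is not excluded, contrary to the written rule.

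The conclusion rests on the inferred formula and on reading the 90% as one-sided. On a two-sided reading the rule would be further off: ln(0.05)/ln(0.78) = 12.06, so 13 patients.

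**What to change.** In the hyponatremia sentence of the sample size section:

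- Change both nines to ten.
- Replace weight gain with hyponatremia in the condition.
- State the attained limits: 0.21 for 0 of 10, and 0.226 for 0 of 9, which does not exclude 22%.

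State that the bound is one-sided, and recompute the companion rules on that basis. For sexual dysfunction, 0 of 10 gives 0.206 instead of 0.31. For weight gain, 0 of 8 gives 0.2501, so nine patients are strictly needed for a rate below 0.25. A single statement would cover all three: with ten evaluable, event-free patients the limit is 0.206, which lies below 0.22, 0.25 and 0.30.

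The cost is wording only. The planned ten patients and all study procedures stay as they are. The one consequence is a slightly stricter hyponatremia rule.
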